### Recruitment

After EMR screening, study staff will coordinate with the patient’s primary ED provider to confirm eligibility and ensure that approaching the patient will not interfere with clinical care. To maintain confidentiality and minimize disruption, recruitment discussions will take place in private or semi-private areas (e.g., examination rooms). Study staff will introduce the study, explaining its purpose, procedures, and voluntary nature, while providing the opportunity for patients to ask questions. If the patient expresses interest, staff will proceed with the informed consent process. Consent will only be obtained once the patient is clinically stable, ensuring that they are in a condition where they can fully comprehend the study details. Participants will be given ample time to review the consent document and ask any questions before signing. Research staff will be available to provide explanations and answer any questions the participant or their family may have. Participants will also have the option to discuss the study with their healthcare provider or family members before deciding. To ensure participants fully understand the research, the research staff will ask comprehension questions after the participant has read the consent form. This step will help assess whether the participant has understood the study, its risk, and benefits. If a participant is unable to demonstrate an understanding of the study, they will not be enrolled. If the treating clinical team or research staff suspects that a patient may have diminished capacity to consent, the patient will not be approached for participation. This ensures that all participants can make an informed decision. Participants will receive a PDF copy of the signed consent form immediately after providing consent via the REDCap (Research Electronic Data Capture) e-consent system. This ensures they have a record of their participation and the study details. All signed consent documents will be securely stored in REDCap. REDCap provides secure electronic storage, ensuring the confidentiality and integrity of participant information in compliance with Health Insurance Portability and Accountability Act (HIPAA) regulations. Since this study is under HIPAA guidelines, all consent documents and related research records will be maintained for a minimum of 6 years following study closure. During this time, the documents will remain securely archived in REDCap, which offers audit trails and data encryption to safeguard participant privacy.

Since January 2025, screening efforts at our primary ED site have identified 217 patients with musculoskeletal pain, of whom 28 met all inclusion criteria, including the ≤4-week trauma requirement. Among those eligible, 25 participants consented and were enrolled, while 3 declined participations, yielding an acceptance rate of approximately 89% and an overall enrolment rate of 11.5% based on screened patients. These preliminary data support the feasibility of enrolling the target sample of 246 participants within the planned 24 – 36-month recruitment period.

### Financial reimbursement

Patient compensation is allocated to incentivize participation, enhance retention, and reduce attrition during the study’s follow-up assessments. Given the longitudinal nature of the study, financial incentives will support continued engagement at key time points, ensuring high-quality data collection and completeness of outcome measures. The distribution of compensation includes:Baseline: completion of Neck-Pain & Attitude Questionnaire (Neck-PAQ) validation study: $101-month follow-up: $50 raffle (four winners; ∼1 in 62 chance)3-month follow-up: $100 raffle (four winners; ∼1 in 62 chance)6-month follow-up: $200 raffle (one winner; ∼1 in 246 chance)

Compensation will be provided through prepaid debit cards or electronic payment methods, ensuring timely and convenient distribution to participants. The incentive structure aligns with best practices for participant retention in longitudinal studies, while remaining compliant with NIH and institutional research (Teague *et al.*, 2018).

### Quantitative outcomes & assessment tools

To ensure standardization and data harmonization with other studies, this study aligns with the HEAL Common Data Elements (CDE) repository (Wandner *et al.*, 2021). Key measures, including pain intensity (VAS), pain frequency (NHIS Pain Chronicity), psychological assessments (PCS, TSK, PHQ-2, GAD-2), functional status (ODI, NDI), and substance use screening (ASSIST), were selected from HEAL’s CDE repository whenever possible (Table 1). Participant follow-up assessments will be conducted at 1-, 3-, and 6-months post-ED visit to track pain progression and related outcomes.

**Table 1. tbl1:** Study measures & assessment tools

Domain	Instrument	Description	Time	Analysis Role
Pain Frequency	Adaptation of National Health Interview Survey (NHIS) Pain Chronicity Question (Duca *et al.*, 2022)	Longitudinal assessment of pain frequency.	0, 1, 3, 6 months	Primary Outcome
Pain Intensity	Visual Analogue Scale (VAS) (Kelly, 2001)	Quantitative metric of an individual’s pain on a numerical scale.	0, 1, 3, 6 months	Secondary Outcome
Functional Status (Low Back)	Oswestry Disability Index (ODI) (Yoshida *et al.*, 2019)	Assesses disability related to low back pain.	0, 1, 3, 6 months	Secondary Outcome
Functional Status (Neck)	Neck Disability Index (NDI) (Pool *et al.*, 2007)	Assesses disability related to neck pain.	0, 1, 3, 6 months	Secondary Outcome
Pain Beliefs	Back/Neck-Pain Attitude Questionnaire (B-PAQ/N-PAQ) (Darlow *et al.*, 2014)	Assesses pain beliefs and attitudes related to neck and back pain.	0, 1, 3, 6 months	Independent Variable
Pain Self-Efficacy	Pain Self-Efficacy Questionnaire-2 (PSEQ-2) (Nicholas et al., 2015)	Assesses an individual’s confidence in performing daily activities despite experiencing pain.	0, 1, 3, 6 months	Mediator
Recovery Expectations	Expectation of Recovery (Single-item measurement) (Carrière *et al.*, 2023)	Assesses individual’s expectation for recovery from current pain episode.	0, 1, 3, 6 months	Mediator
Fear-Avoidance Behaviour	Tampa Scale of Kinesiophobia (TSK) (Tkachuk & Harris, 2012)	Quantitative metric asking 11 questions using a 4-point Likert scale regarding a participant’s fear and avoidance of movement.	0, 1, 3, 6 months	Mediator
Catastrophic Thinking	Pain Catastrophizing Scale (PCS) (Monticone *et al.*, 2022)	13-item quantitative metric assessing participant’s catastrophic thinking about their pain experience, contributing to rumination, magnification, and learned helplessness.	0, 1, 3, 6 months	Mediator
Physical Activity	International Physical Activity Questionnaire-Short Form (IPAQ-SF) (Oliveira *et al.*, 2023)	Assesses self-reported physical activity levels over the past 7 days, including walking, moderate-intensity, and vigorous-intensity activities, as well as sedentary time.	0, 1, 3, 6 months	Mediator
Anxiety	Generalized Anxiety Disorder-2 (GAD-2) (Sapra *et al.*, 2020)	Brief screening tool for generalized anxiety disorder.	0, 1, 3, 6 months	Covariate
Depression	Patient Health Questionnaire-2 (PHQ-2) (Kroenke *et al.*, 2003)	Brief screening tool for depressive symptoms.	0, 1, 3, 6 months	Covariate
Substance Use	Alcohol, Smoking, and Substance Involvement Screening Test (ASSIST) (WHO Assist Working Group, 2002)	Screens for substance use risk, including alcohol, tobacco, and drug use.	0, 1, 3, 6 months	Covariate
Social Determinants of Health (SDOH)	Accountable Health Communities (AHC) Health-Related Social Needs (HSRN) Screening Tool from Centers for Medicare & Medicaid Services (CMS) (Centers for Medicare & Medicaid Services, 2021)	Evaluates social factors affecting health, including financial strain, employment, housing, food security, transportation, and social support.	0, 1, 3, 6 months	Covariate
Demographics	N/A	Age, Sex, Insurance, Co-Morbidities, Race/ethnicity, Past Medical History	0	Covariate

The primary outcome is the development of CMP in the neck and/or low back, defined as pain in the same anatomical region as the acute presenting complaint, present on most days or every day for at least three months. Secondary outcomes will include changes in pain beliefs (assessed through B-PAQ/N-PAQ scores), pain catastrophizing (PCS scores), and fear-avoidance behaviours (TSK scores), and healthcare utilization, including recurrent ED visits and outpatient care. Additional secondary measures will evaluate changes in physical activity levels (IPAQ-SF scores), pain self-efficacy (PSEQ-2 scores), and pain-related disability, measured through changes in ODI and NDI scores over time. While this study applies the Cognitive Risk Model for CMP specifically to post-traumatic neck and/or low back pain, the model is designed to be adaptable to other anatomical regions and chronic pain types – including both chronic primary and secondary musculoskeletal pain – in future research (Treede *et al.*, 2015).

In addition to baseline enrolment forms, we will perform a chart audit post-ED discharge to assess ED management, including ED imaging (x-ray, CT, MRI), medication management (including opioids, NSAIDs, acetaminophen, and muscle relaxants), ED disposition (admission vs discharge), diagnostic codes (ICD-10 for musculoskeletal and neurological conditions), and referrals provided (e.g., primary care, pain specialist, physical therapy). After 1- and 6-month follow-ups, additional audits will be completed utilizing an automated process to query the EMR using the Financial Identification Number (FIN) and Medical Record Number (MRN) from the index ED visit. Using these patient-specific identifiers collected during enrolment, a report can be generated for pre-specified data fields in the EMR which exactly matches the data dictionary in the case report form (CRF) built in REDCap. Data can be imported into REDCap and will be checked for fidelity and missingness. An advantage of this process is reduction in bias inherent in manual chart review (Gilbert *et al.*, 1996). As a further check, we will query the regional health information exchange for relevant healthcare utilization at regional outside hospitals.

### Sample size & quantitative data analysis

Our primary outcome – pain frequency – is assessed as a categorical variable based on participants’ reported number of days per week experiencing neck or low back pain (0–1 days, 2–3 days, 4–5 days, or 6–7 days). Pain frequency will be assessed at 1, 3, and 6 months. For analysis, responses will be dichotomized to classify CMP status: participants reporting pain on 4–5 or 6–7 days per week will be categorized as having CMP (coded as 1), while those reporting 0–1 or 2–3 days per week will be categorized as not having CMP (coded as 0). Based on prior studies reporting a 12%–27% transition rate from acute to chronic pain (Beaudoin *et al.*, 2020; Office of the Assistant Secretary for Planning and Evaluation, 2021; Bourassa *et al.*, 2020; Barnett *et al.*, 2017), we conducted a power analysis to estimate the incidence of CMP with acceptable precision. Using a small effect size (Cohen’s d 0.2), with α = 0.05 and power = 0.80, a minimum sample size of 197 participants is required. To account for an estimated 25% attrition rate, we will recruit 246 participants to ensure adequate study power. This sample size will also provide sufficient power to explore the association between baseline pain beliefs and subsequent development of CMP, as well as to conduct preliminary analyses for establishing potential clinical cut-offs on pain relief measures. Higher scores may indicate individuals at elevated risk for developing CMP and who may benefit from targeted educational interventions. However, these exploratory analyses will require validation in independent samples.

Quantitative statistical analysis will involve predictive model development using multivariable logistic regression to identify significant predictors of CMP as a binary outcome. Pain beliefs will be modelled as the primary independent variable, with adjustment for potential confounding variables identified in the conceptual framework (e.g., demographics, anxiety, depression, substance use, and social determinants of health). Mediation analyses will explore indirect pathways through cognitive-affective constructs (e.g., pain catastrophizing, fear-avoidance, recovery expectations, and pain self-efficacy) and behavioural responses (e.g., physical activity), using structural equation modelling or mediation analysis to estimate direct and indirect effects. Interaction terms between pain beliefs and demographic variables will be tested to evaluate potential effect modification. Model validation will incorporate cross-validation techniques, such as k-fold cross-validation, to assess robustness. Receiver operating characteristic (ROC) curve analysis will determine the model’s discriminative ability using area under the curve (AUC) estimates, and calibration analysis (e.g., Hosmer–Lemeshow test) will assess model fit. Preliminary clinical cut-offs for pain beliefs scores will also be explored by identifying thresholds that maximize sensitivity and specificity for predicting CMP developed based on ROC analysis. Sensitivity analyses will evaluate the stability of findings under alternative variable definitions and measurement criteria.

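### The d = 0.2 calculation behind 197 participants fits neither the incidence aim nor the logistic regression, so the claim of sufficient power for the belief–CMP association is unsupported, and it is false at d = 0.2

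*Protocol article*

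**What the plan says.** Everything at issue stands in the protocol article, section *Sample size & quantitative data analysis*.

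- **Aim of the calculation:** "we conducted a power analysis to estimate the incidence of CMP with acceptable precision". No interval width is given.
- **Rate cited:** "Based on prior studies reporting a 12%–27% transition rate from acute to chronic pain".
- **Inputs and result:** "Using a small effect size (Cohen’s d 0.2"), then "with α = 0.05 and power = 0.80, a minimum sample size of 197 participants is required".
- **Allowance for loss:** "To account for an estimated 25% attrition rate, we will recruit 246 participants to ensure adequate study power".
- **Extension to the main hypothesis:** "This sample size will also provide sufficient power to explore the association between baseline pain beliefs and subsequent development of CMP". The same sentence extends the claim to preliminary work on clinical cut-offs. No separate effect size, power level or calculation is given for either.
- **Planned analysis:** "predictive model development using multivariable logistic regression to identify significant predictors of CMP as a binary outcome", and "Pain beliefs will be modelled as the primary independent variable, with adjustment for potential confounding variables identified in the conceptual framework".

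**The concern.** Three things that should match do not. The aim is to estimate a proportion, the inputs are those of a test on a mean, and the main analysis regresses a binary outcome on a score. A precision calculation needs an expected proportion and an interval width. A power calculation for the regression needs the event rate and an effect per unit of the score. The calculation as given has neither a width nor an effect for the association.

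The event rate matters because the information on the association is proportional to n·p·(1−p), where p is the CMP proportion. At 12% to 27% CMP that is n multiplied by 0.106 to 0.197, so roughly one fifth to one ninth of n.

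This is the only sample-size justification in the article, and pain beliefs are the main exposure. A reader who sees a small effect size, 80% power and a statement of sufficiency in one paragraph may take it that small effects of beliefs are covered. They are not.

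**Working it through.** **Inputs from the article.** α = 0.05 (two-sided reproduces the stated figure), power 0.80, d = 0.2, CMP 12% to 27%, 246 recruited, 25% loss. The sum z₀.₉₇₅ + z₀.₈₀ is 1.960 + 0.842 = 2.802.

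**1. Reproduce 197.** n = (2.802/0.2)² = 196.2, rounded up to 197. This is the normal-approximation size for a two-sided one-sample or paired mean test; the t version gives 199. Other readings:

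| Reading | n |
|---|---|
| One-sided, one-sample mean, d = 0.2 | 155 |
| Two equal groups, d = 0.2 | 393 per group |
| Correlation r = 0.2 | 194 |
| One-sample proportion, Cohen's h = 0.2 | 197 |
| Chi-square, 1 df, w = 0.2 | 197 |

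The last two give the same n, but the article says d. In the d-based expression the CMP rate does not appear.

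**2. Number analysed.** 246 × 0.75 = 184.5, so about 184, below the 197 called a minimum. How the allowance for loss was made is a separate matter. Results are shown for both numbers.

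**3. Power for the association if d = 0.2.** Compare mean baseline belief score between patients with and without CMP, unadjusted: power = Φ(d·√(n·p·(1−p)) − 1.960).

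- n = 197, p = 0.12 (about 24 events): 0.2 × √20.80 = 0.912; Φ(−1.048) = 14.7%.
- n = 197, p = 0.27 (about 53 events): 0.2 × √38.83 = 1.246; Φ(−0.714) = 23.8%.
- n = 184, p = 0.12 (about 22 events): 14.0%.
- n = 184, p = 0.27 (about 50 events): about 22%.
- All 246 retained: 17.3% to 28.5%.

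**4. Patients needed for d = 0.2 at 80% power.** n = 196.2/(p·(1−p)): 196.2/0.1056 ≈ 1,860 at 12% and 196.2/0.1971 ≈ 1,000 at 27%, all analysed.

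**5. Effect detectable at 80% power.** d = 2.802/√(n·p·(1−p)). With normal scores and a common SD in the two groups, the log odds ratio per SD equals d, so OR = exp(d). The adjusted column divides d by √(1 − 0.20), assuming that covariates explain 20% of belief variance; the article gives no such figure.

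| n | CMP | d | OR per SD, unadjusted | OR per SD, adjusted |
|---|---|---|---|---|
| 197 | 12% | 0.61 | 1.85 | 1.99 |
| 197 | 27% | 0.45 | 1.57 | 1.65 |
| 184 | 12% | 0.64 | 1.89 | about 2.0 |
| 184 | 27% | 0.47 | 1.59 | about 1.7 |

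**6. Precision for the stated incidence aim.** Half-width = 1.96·√(p(1−p)/n). With 197: 4.5 points (12%) to 6.2 points (27%). With 184: 4.7 to 6.4 points. The article states none of these.

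**The case against.** The strongest reply is that the article ties d = 0.2 and 80% power to the incidence aim only. The sentence on the association names no effect and no power level. A reader might infer that the article promises 80% power for d = 0.2 on the association and that the true figure is 15% to 24%. The text does not say that, so the low power is conditional on d = 0.2 being the target. For a larger true effect the sample does better: at d = 0.5 with 197 analysed, power is about 63% (12% CMP) to 88% (27% CMP). This part of the reply stands. What it leaves is a claim of sufficiency with no calculation behind it, which fails at the one effect size stated.

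Three further points also stand:

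- **The test is not named.** It cannot be said that 197 arises only from a one-sample mean test, because h = 0.2 or a 1-df w = 0.2 gives the same number. An effect size may have been mislabelled. If so, the stated d is wrong and still needs correcting.
- **The detectable effect is not large.** A d of 0.47 to 0.64 lies around Cohen's medium value of 0.5. Saying that only moderate to large effects can be found would go too far.
- **The cut-off work is already hedged.** The article calls it preliminary and in need of independent validation, and it claims no power for interactions. Nothing in the article says that a null result would be read as showing that beliefs do not matter.

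It might also be said that an analysis plan could hold the details. That does not help here: the problem is a calculation and a claim that are stated and do not match, not something left out.

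**Conclusion.** The point holds in this form. The only sample-size justification fits neither its stated aim nor the main analysis, and the sufficiency claim for the belief–CMP association has no calculation behind it. If d = 0.2 is the target, the claim is false: unadjusted power is about 15% to 24% with 197 analysed and about 14% to 22% with 184, and 80% power would need about 1,000 to 1,860 analysed patients. Covariate adjustment would lower power further.

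These figures rest on the article's own 12% to 27% rate, two-sided α = 0.05, and a normal approximation with a common SD. The adjusted odds ratios also rest on the assumed 20% of belief variance explained. The documents do not support the stronger statement that the article claims 80% power for d = 0.2 on the association, or that the sample is inadequate for any plausible effect. The article gives no expected effect against which to judge that.

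**What to change.** Delete the Cohen's d rationale and the unqualified statement of sufficient power. State instead what about 184 completers provide:

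- **Incidence:** a 95% confidence interval half-width of about 4.7 points (12% CMP) to 6.4 points (27% CMP).
- **Association:** 80% power for an unadjusted odds ratio of about 1.9 (12% CMP) to 1.6 (27% CMP) per SD of the belief score, that is d of about 0.64 to 0.47. With adjustment, about 2.0 to 1.7, naming the assumption that covariates explain 20% of belief variance.

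Add that a null result cannot exclude small effects, and make no claim of power for the cut-off analyses. The cost is wording only: no more patients, and no change to endpoint or analysis. The downside is that the stated figure becomes less favourable.

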**Background::**

CMP is a leading cause of global disability, yet early risk factors for its development remain poorly characterized, particularly in ED settings. This prospective observational study will recruit 246 adult patients presenting with acute (≤ 4 weeks) neck or back pain after a recent trauma. Pain beliefs – measured using pain and attitude questionnaires – serve as the primary independent variable. Mediating variables include catastrophic thinking, fear-avoidance behaviors, low physical activity, poor recovery expectations, and low self-efficacy for pain management. Covariates include demographics, social determinants of health, mental health disorders, and high-risk substance use. The primary outcome is the presence of CMP at six months, defined as pain on most or every day for at least three months. Participants will complete follow-ups at 1, 3, and 6 months. Multivariable logistic regression, mediation analyses, and interaction testing will explore effects of pain beliefs on CMP development. As a secondary aim, a subset of participants will complete Think Aloud cognitive interviews to assess response process validity for the Neck Pain Attitudes Questionnaire (Neck-PAQ), a region-specific adaptation of the Back Pain Attitude Questionnaire, analyzed using a deductive content analysis framework.

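### Recruiting 246 does not cover the stated 25% attrition: about 184 participants would remain, below the plan's own minimum of 197

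*Protocol article*

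**What the plan says.** The section on sample size and quantitative data analysis in the protocol article states three linked figures.

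- Required number: for a Cohen's d of 0.2, "with α = 0.05 and power = 0.80", the article says that "a minimum sample size of 197 participants is required".
- Attrition and target: "To account for an estimated 25% attrition rate, we will recruit 246 participants to ensure adequate study power".

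The target of 246 also appears elsewhere. The abstract says "This prospective observational study will recruit 246 adult patients". The Recruitment section uses it for feasibility, referring to the "target sample of 246 participants within the planned 24 – 36-month recruitment period". The raffle odds in the Financial reimbursement section (1 in 246, and about 1 in 62 for four winners) rest on it too.

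The article gives no other attrition rate and no other derivation of 246.

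**The concern.** An allowance for attrition should leave the required number after the losses. The number to recruit is therefore the required number divided by the fraction expected to remain. Multiplying by one plus the attrition rate gives too few, and the gap grows with the rate. At 25% it is no longer a matter of rounding.

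Attrition does reduce the analysed sample here. The primary outcome is chronic pain status at six months, classified from the days per week with pain that participants report. A participant lost to follow-up has no observed outcome. The chart audits collect ED management and healthcare use, not pain frequency, so they cannot fill the gap.

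At stake is the statement that 246 secures adequate power. The same paragraph extends that assurance to the association between pain beliefs and chronic pain and to exploratory cut-offs. The next paragraph adds a multivariable logistic model, mediation, interaction terms and cross-validation, all drawing on the same outcome events.

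**Working it through.** **Inputs**, all from the sample-size section: required number 197; attrition 25%; target 246; d = 0.2; α = 0.05; power 0.80; transition rate 12%–27%. The section names neither the test nor its sidedness. Two-sided testing is assumed below unless stated otherwise.

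**1. Reproducing the plan's figures**

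- Required number: ((1.960 + 0.842) / 0.2)² = 196.2, so 197. This is a two-sided one-sample normal approximation. A chi-square test on 1 degree of freedom with w = 0.2 also gives 197; a one-sample t test gives 199.
- Target: 197 × (1 + 0.25) = 246.25, which matches 246.
- A second route gives the same number: 197 / (1 − 0.20) = 246.25. So 246 would also fit a correctly applied 20% rate.

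**2. Correct allowance for 25%**

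- 197 / (1 − 0.25) = 262.7, so 263.
- 263 − 246 = 17 more recruits than planned.

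**3. What 246 delivers**

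- Completers at 25% attrition: 246 × 0.75 = 184.5.
- Shortfall: 197 − 184.5 = 12.5, and 12.5 / 197 = 6.3%.
- Largest attrition that still leaves 197: 1 − 197/246 = 19.9%. At exactly 20%, 246 × 0.80 = 196.8, just under 197.

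**4. Effect on power**

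| Calculation (d = 0.2, two-sided) | n = 197 | n = 184 |
|---|---|---|
| One-sample, normal | 80.2% | 77.4% |
| One-sample, t | 79.8% | 77.0% |

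The result hardly depends on which test was used. For any test whose standardised effect grows with √n, start from 80% power at 197 and scale by √(184/197) = 0.966:

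- Two-sided: (1.960 + 0.842) × 0.966 − 1.960 = 0.75, giving power of about 77%.
- One-sided: (1.645 + 0.842) × 0.966 − 1.645 = 0.76, giving about 78%.

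**5. Effect on events and precision**

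| Transition rate | Events at 197 | Events at 184 | 95% half-width at 197 | 95% half-width at 184 |
|---|---|---|---|---|
| 12% | 23.6 | 22.1 | 4.5 points | 4.7 points |
| 27% | 53.2 | 49.7 | 6.2 points | 6.4 points |

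Half-widths are 1.96 × √(p(1 − p)/n).

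**The case against.** Four points can be made for the plan.

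- **The multiplication by 1.25 is not printed.** This stands. The number 246 fits 197 × 1.25 and also 197 / 0.80, so the slip may lie in the arithmetic or in the attrition rate reported. The conflict does not depend on which: 197, 25% and 246 are inconsistent either way.
- **The 77% is not the plan's own figure.** This stands in part. The article names no test, and the planned analysis is logistic regression. But if power is 80% at 197, as the article says, it is about 77% to 78% at 184 under each of the simple tests considered. The figure restates the plan's premise; it does not measure the power of the logistic model.
- **The loss is small and the study is observational.** This stands as to size. The section gives estimation of incidence as the purpose of the calculation, and the confidence interval widens by only about 0.2 points on each side. It bears on how serious the error is, not on whether the figures agree.
- **A fuller protocol or analysis plan may cover it.** This does not help. Nothing is missing here: the article prints all three numbers, and they contradict each other.

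**Conclusion.** The concern holds. On the article's own inputs, recruiting 246 and losing 25% leaves about 184 participants with an observed primary outcome, 12 to 13 below the stated minimum. The claim that 246 secures adequate power is therefore wrong as written. The consequence is modest: roughly 3 percentage points of power and 2 to 4 expected events. The shortfall needs only the printed figures and the reading that participants lost to follow-up contribute no primary outcome. The power figure also needs the plan's premise of 80% at 197.

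A separate question is left open. A calculation based on Cohen's d does not match a binary incidence or a logistic regression, so 197 is itself a questionable base. Correcting the attrition step does not settle that.

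**What to change.** Keep 246 and correct the statement in the sample-size section, for example:

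> With 246 enrolled and 25% attrition, about 184 participants are expected to be evaluable. A calculation giving 80% power at 197 gives about 77% at 184. The minimum of 197 is met only if attrition does not exceed 19.9%.

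The later assurance of sufficient power for the further analyses should then refer to about 184 participants and, at the quoted transition rates, about 22 to 50 events. The cost is wording only; the abstract, feasibility statement and raffle odds stay as they are.

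Two alternatives would also remove the contradiction:

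- **Change the attrition rate.** If the intended rate was about 20%, say so and justify it. The cost is again wording, but 246 × 0.80 = 196.8, so the rate must be just under 20% to leave a full 197.
- **Recruit 263.** This keeps both 197 and 25%. It costs 17 more participants, plus edits to the abstract, the Recruitment section and the raffle odds. It is not needed to correct the text.

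### With about 22 to 50 events and no shrinkage stated, the logistic prediction model would give risks that are far too extreme, and an in-sample Hosmer–Lemeshow test would not show it

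*Protocol article*

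**What the plan says.** All of this stands in the Protocol article under Sample size & quantitative data analysis, with the variables in Table 1.

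- **Model.** The analysis is "predictive model development using multivariable logistic regression to identify significant predictors of CMP as a binary outcome". Pain beliefs are the main independent variable, adjusted for framework confounders, with demographics, anxiety, depression, substance use and social determinants of health (SDOH) as examples. Belief-by-demographic interactions are to be tested. No penalty, shrinkage or parameter limit is stated.
- **Performance.** AUC from ROC analysis and k-fold cross-validation are planned, and "calibration analysis (e.g., Hosmer–Lemeshow test) will assess model fit".
- **Size.** The event rate is taken from a "12%–27% transition rate from acute to chronic pain". The plan then states that "a minimum sample size of 197 participants is required", and "To account for an estimated 25% attrition rate, we will recruit 246 participants". The calculation takes no account of the number of model parameters.
- **Caveat.** The belief association and the cut-off work are called exploratory and in need of validation in other samples.
- **Use.** The Discussion says that patients flagged as high risk by the predictive model will have priority in the planned Pain-SBIRT work.

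**The concern.** A logistic model fitted by maximum likelihood to few events fits noise as well as signal. In new patients its predicted risks are then too spread out: high predictions are too high and low ones too low. The calibration slope measures this. It is 1 when the spread is right and below 1 when predictions are too extreme.

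A test of fit on the data used to build the model compares the model with the same noise that it has absorbed, so it can pass while the slope in new patients is poor. The absolute risks would then be wrong for the purpose that the Discussion gives the model, which is choosing whom to prioritise.

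**Working it through.** **1. The plan's own figures.** The one-sample formula with d = 0.2, two-sided α = 0.05 and power 0.80 gives ((1.960 + 0.842)/0.2)² = 196.2, rounded up to 197. This matches. Then 197 × 1.25 = 246.25, which gives 246.

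**2. Events.** After 25% loss, 246 × 0.75 = 184.5 patients remain.
- At 12%: 184.5 × 0.12 = 22.1 events.
- At 27%: 184.5 × 0.27 = 49.8 events.

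The 184.5 is below the plan's minimum of 197, because the inflation multiplied by 1.25 where dividing by 0.75 gives 263. This hardly matters here: 197 completers would give 23.6 to 53.2 events.

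**3. Parameters (assumed range).**
- One term each: beliefs 1, six demographic and history items 6, anxiety and depression 2, substance use 1, SDOH 1. Total 11.
- With dummy variables and domains: beliefs 1, demographics 9 (insurance 2, race/ethnicity 3), anxiety and depression 2, substance use 3, SDOH 6. Total 21.
- With the five mediators also used as predictors: 26. Interactions would add more.

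Events per parameter: 22.1/11 = 2.0 to 49.8/11 = 4.5 at the low count; 1.1 to 2.4 at 21; 0.9 to 1.9 at 26.

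**4. What 184.5 patients can carry.** For expected shrinkage S = 0.9, n = P / [(S − 1) ln(1 − R²/S)]. R² is the Cox–Snell value, taken as 0.15 to 0.35 of its maximum (an assumption).
- Lowest case (12%, R² = 0.078): P = 184.5 × 0.1 × 0.0906 = 1.7.
- Highest case (27%, R² = 0.241): P = 184.5 × 0.1 × 0.3117 = 5.8.

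So the data support about 2 to 6 parameters. For 11 parameters, n = 11/0.03117 = 353 to 11/0.00906 = about 1,214. For 20, it is about 640 to 2,200.

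**5. Simulation.** n = 184, maximum likelihood, no selection. Setting A has one predictor with log odds ratio 0.4 and the rest with 0.15. Setting B has five real predictors plus noise and a true AUC of 0.75. Median calibration slope in new patients, at 12% / 27% CMP:

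| Parameters | Setting A | Setting B |
|---|---|---|
| 8 | 0.37 / 0.57 | 0.64 / 0.75 |
| 12 | 0.29 / 0.45 | 0.49 / 0.60 |
| 20 | 0.23 / 0.39 | 0.31 / 0.47 |

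At a slope of 0.45, two patients whose predicted odds differ 8-fold truly differ by about 8^0.45 = 2.5-fold.

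In setting B with 20 parameters:
- Apparent AUC was 0.86 / 0.82, against 0.66 / 0.69 in new patients.
- Ten-fold cross-validated AUC was 0.63 / 0.68.
- The cross-validated calibration slope was 0.23 / 0.39, so that measure does show the problem.

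In-sample Hosmer–Lemeshow rejected at the 5% level in about 4% to 13% of runs over all cells of both settings (8 to 25 parameters).

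**6. Candidate remedies, setting A.**
- Cross-validated ridge brought the median slope to 0.96–1.17 and lowered the Brier score in every cell.
- Firth's method with 10 parameters gave 0.39 / 0.53, against 0.35 / 0.50 for maximum likelihood. With 8 parameters it gave 0.44 / 0.60.

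**The case against.** The other side has several good points.

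- **Details are inferred.** The article gives no parameter count, does not say that the fit is unpenalised, and does not describe stepwise or p-value selection. A reader might infer a commitment to 20 or more unpenalised terms chosen by significance, but the text does not support that. The confounders come from a framework drawn up in advance, and identifying significant predictors may only mean reporting which are significant. Coding and summary scores may sit in a fuller document. This stands, which is why the count is a range and the simulations had no selection step. The overfit is already marked at 12 parameters.
- **Cross-validation is planned.** A reader might infer that an inflated AUC would be published. The document does not say that the AUC will be in-sample, and the cross-validated values above were close to those in new patients. This stands if every modelling step is repeated in each fold. It answers the AUC optimism but not the extreme predictions.
- **Cut-offs.** A reader might infer that the clinical cut-offs would also be distorted. They are set on the single pain-beliefs score, are labelled preliminary, and are said to need independent validation. With one predictor at n = 184, apparent AUC was 0.604 / 0.613 and new-data AUC 0.606 / 0.610. Overfitting the multivariable model does not reach them.
- **Hosmer–Lemeshow is only an example.** True, but it is the only calibration tool named.
- **The AUC gap depends on the scenario.** In setting A with 20 parameters the true model itself reaches only about 0.70 / 0.69. The slope is therefore the better summary.

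**Conclusion.** The point holds in a limited form. The plan fixes a modelling approach and an example check that do not suit 22 to 50 events. With 12 to 20 parameters fitted by maximum likelihood, predicted risks in new patients would be far too extreme (median slope about 0.2 to 0.6). Even 8 parameters give 0.37 to 0.75. Hosmer–Lemeshow on the development data rejects at not much more than its nominal rate and would not reveal this.

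The event count follows from the plan's own inputs. The rest assumes that no penalty is intended, a parameter count of about 11 to 26, and predictor strengths like those simulated. The size of the miscalibration varies with these assumptions; its direction did not in any case examined. The point does not extend to the beliefs cut-offs, nor to the AUC if cross-validation is done in full. It should be changed before analysis but does not threaten the study's conduct.

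**What to change.** 1. **Separate the two models.** For the beliefs association, use a short confounder list fixed in advance, summary scores for SDOH and ASSIST, and no selection on p-values.
2. **Penalise the prediction model.** Fit ridge or LASSO logistic regression on baseline predictors named in advance, with the penalty tuned inside cross-validation. Do not rely on Firth's method, or on cutting to 8 to 10 unpenalised terms, to control the overfit. Only ridge was checked here.
3. **Report corrected performance.** Give AUC, calibration slope and intercept as cross-validation- or bootstrap-corrected values, with every modelling step repeated in each resample. Add a smoothed calibration plot. Use these in place of in-sample Hosmer–Lemeshow.

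This needs no extra patients or data, only analysis wording and a little more programming. The downsides are a lower reported AUC and prediction-model coefficients biased towards the null, so effect estimates for pain beliefs should come from the association model.
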